### Quality control

Datamanagement of this study will be conducted by the Netherlands Comprehensive Cancer Organisation (IKNL). Quality of data entry will be ensured through the electronical medical record, in which validation messages for users are created. In this way, a message will be shown to the data managers when something is incorrectly filled in (for example: date in the past or future, unreliable low or high patient age). Furthermore, the conduct of the MATILDA-trial will be supervised through on-site monitoring. An initiation monitor visit will be planned for all participating centers at the start of the inclusion period. Second, every center will be visited by an independent monitor after the first five included patients, and will be checked on withdrawal of informed consent, source data verification, whether inclusion and exclusion criteria are correctly followed and whether SAE’s are correctly reported. On-site monitoring later in the trial will be done if necessary. In this way, high quality will be ensured throughout the study.

### Study integrity

The medical ethical committee of the UMC Utrecht has reviewed the study in accordance with the Dutch Medical Research Involving Human Subjects Act (WMO) and other applicable European regulations and has granted a positive judgement. In addition, this study protocol has been peer reviewed by external reviewers from the Dutch Cancer Society (KWF Kankerbestrijding), the funder of this trial.

### Sample size calculation

The sample size is calculated for the primary outcome parameter recurrence rate at 6 months. Sample size for recurrence rate is calculated based on the assumption that the recurrence rate is 2 % in the ESD group and 12 % in the EMR group [8, 10, 16]. With a power of 80 % and a two-sided α of 0.05, the total number of patients needed is 198. To correct for patients lost-to-follow-up (7 %), a final total of 212 patients will be included; 106 patients in each arm.

### Data analysis

Primary analyses will be conducted on the intention-to-treat principle. Normally distributed continuous variables will be expressed as mean (± standard deviation) and not-normally distributed variables will be expressed as median (interquartile range). Categorical data will be presented with percentages. The outcome measures recurrence rate, R0-resection rate, surgical referral rate, and complication rate will be compared using a stratified analysis with a test for binary outcomes. For the perceived burden and quality of life analysis, data will be collected, presented and compared according to the user guides for the selected questionnaires [19, 24, 25, 28]. QALY estimates for the first 6-month follow-up period (i.e. short-term) and the 36-month follow-up period (i.e. long-term) will be calculated for both arms, using the Dutch tariff and the self-reported EQ-indexes at the different contact moments [29]. An area under the curve (AUC) approach will be followed by interpolating between the observations provided by the patients. Effects will be discounted at 1.5 %, according to current Dutch economic guidelines [30, 31]. QALY estimates will be compared between both arms using non-parametric test when not normally distributed. Healthcare costs will be calculated by multiplying used healthcare services by the appropriated unit cost prices. Own bottom-up micro costing will be applied for ESD, EMR and colonoscopies. For all other healthcare services reference prices will be used, where available [30, 31]. Costs will be discounted with 4 % according to current Dutch economic guidelines [30–32]. All costs will be expressed in 2018 euros. The actual healthcare costs occurring in both arms will be compared for the 6-month follow-up (i.e. short-term) and the 36-month follow-up (i.e. long-term), respectively. Costs estimates will be compared between both arms using a non-parametric test. A *p*-value of < 0.05 will be considered significant.

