#### Secondary outcomes

Radical (R0-)resection rate. This is defined as dysplasia free vertical and lateral resection margins at histology.Perceived burden and quality-of-life (QoL) among patients at 36 months. This will be assessed using questionnaires. A summary of the investigated domain and type of questions can be found in Table 2. In short, colorectal cancer anxiety is measured at baseline, 4 days and 4 weeks after ESD/EMR, and after the 6 and 36 months follow-up colonoscopy using an instrument originally designed and validated in breast cancer patients, and subsequently used to evaluate patients’ perception of colorectal cancer risk [19, 20]. Burden of the procedure will be measured on day 4 after ESD/EMR and after the 6 months follow-up colonoscopy using an instrument proven to be a reliable and valid assessment in prior studies [21–23]. Functional complaints will be measured at baseline, 4 weeks after ESD/EMR, and after the 36 months follow-up colonoscopy using the Colorectal Function Outcome (COREFO) instrument [24]. Quality-of-life will be measured at baseline, 4 days and 4 weeks after EMR/ESD, after the 6 months follow-up colonoscopy, 13 months after EMR/ESD, and after the 36 months follow-up colonoscopy using the EQ-5D-5L-instrument [25]. The EQ-5D, developed by the EuroQol group, will be used to calculate quality adjusted live years (QALYs) and consists of two parts, the EQ-5D descriptive system and the EQ visual analogue scale (EQ-VAS). The EQ-VAS records the participant’s self-reported health on a VAS from 0 (labeled “worst imaginable health state”) to 100 (labeled “best imaginable health state”). The EQ-5D descriptive system consists of five domains (i.e. mobility, self-care, usual activities, pain/discomfort and anxiety/depression) and five functioning levels (i.e. no problems, slight problems, moderate problems, severe problems or unable to function). The questionnaires will be send digital to the participating patients by Castor EDC (CIWIT b.v.). A reminder will be send when participants don’t respond. Patients who prefer to complete the forms on paper will receive the questionnaires by mail.

**Table 2 Tab2:** Patients’ perceived burden and quality of life assessment

	Item	N	Method of measurement	Scale
Patients’ perception of treatment	Burden of the procedure	3	Verbal measure	5-point scale
	Burden afterwards	3	Verbal measure	5-point scale
	Overall perception	1	VAS	1-10

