### Economic evaluation

In the economic evaluation, the balance between costs and effects will be assessed between both arms on both short (i.e. 6 months) and long-term (i.e. 36 months). Results of both cost and effect measurement will be integrated and expressed as incremental cost-effectiveness ratios (ICER) showing additional costs per recurrence free patient and as ICER showing incremental costs per incremental QALY. Both sensitivity and scenario analyses will be conducted. Sensitivity analysis will be conducted for uncertain parameters, and scenario analysis will be used to model for example the impact of anticipated changes of reduced frequency or prolonged interval of follow-up colonoscopies after R0-resection.

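### The QALY comparison names no adjustment for the baseline EQ-5D the trial collects: unbiased on average, but less precise and exposed to the chance baseline difference

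*Protocol article*

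**What the plan says.** The Secondary outcomes section sets the EQ-5D-5L schedule: "Quality-of-life will be measured at baseline, 4 days and 4 weeks after EMR/ESD, after the 6 months follow-up colonoscopy, 13 months after EMR/ESD", and again after the 36-month colonoscopy.

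The Data analysis section then builds the QALYs: "QALY estimates for the first 6-month follow-up period (i.e. short-term) and the 36-month follow-up period (i.e. long-term) will be calculated for both arms". The construction is described as follows: "An area under the curve (AUC) approach will be followed by interpolating between the observations provided by the patients". It adds: "Effects will be discounted at 1.5 %, according to current Dutch economic guidelines".

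For the comparison of arms it says: "QALY estimates will be compared between both arms using non-parametric test when not normally distributed". No covariate is mentioned, and no method is given for the case in which QALYs do look normal. The same section is more specific about the binary endpoints, a list that ends: "surgical referral rate, and complication rate will be compared using a stratified analysis with a test for binary outcomes". QALYs are not in that list.

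The Economic evaluation section combines the cost and effect results into two ratios, one per recurrence-free patient and one per QALY. It does not say how the incremental QALY is estimated. Its sensitivity and scenario analyses do not mention baseline utility. Under Recruitment and randomization, the strata are polyp size, location and center; baseline utility is not one of them.

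**The concern.** A patient who starts with a low EQ-5D index tends to stay low, so part of the spread in 36-month QALYs was already visible at baseline. A plain two-arm test leaves that part in the error term. It also leaves in the estimate whatever difference in baseline utility the randomisation happened to produce.

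Cost-effectiveness at 6 and 36 months is part of the trial's stated aim, and the QALY difference is the denominator of one of its two ratios. A ratio of this kind needs a difference in means. A non-parametric test as usually applied gives a p-value but neither that mean difference nor a baseline adjustment. The variable needed to do better is already in the database.

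**Working it through.** **Inputs from the protocol article.** EQ-5D-5L at baseline, 4 days, 4 weeks, 6, 13 and 36 months; area under the curve by interpolation; effects discounted at 1.5%; 198 patients before allowance for loss to follow-up, hence 99 per arm.

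The documents state no QALY figure to reproduce. The 198 reproduces with the unpooled formula for two proportions: (1.96 + 0.8416)² × (0.12 × 0.88 + 0.02 × 0.98) / 0.10² = 98.27, so 99 per arm.

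**Assumptions, not in the documents.** EQ-5D SD 0.20 at every visit; equal correlation ρ between any two visits, 0.3 to 0.7; 99 evaluable per arm.

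**Step 1: weight of each visit.** Linear interpolation with 1.5% yearly discounting gives these weights in years: baseline 0.0055, day 4 0.0383, week 4 0.2438, month 6 0.4992, month 13 1.2219, month 36 0.9253; total 2.934. The baseline value's own share is 0.0055 / 2.934, about 0.2% (1.1% at 6 months, 0.0055 / 0.498). The area therefore owes almost nothing directly to the baseline value.

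**Step 2: carry-over through correlation.** The expected change in 36-month QALYs per unit of baseline index is 0.0055 + ρ × (2.934 − 0.0055). That is 0.88, 1.47 and 2.06 for ρ = 0.3, 0.5 and 0.7.

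**Step 3: size of a chance baseline difference.** Its standard error is 0.20 × √(2/99) = 0.028. With SD 0.15 to 0.25 it is 0.021 to 0.036.

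**Step 4: effect on the QALY difference.** The sum of the squared weights is 2.659, and the square of their total is 8.608. The variance of a patient's QALYs is 0.20² × [(1 − ρ) × 2.659 + ρ × 8.608]. The unadjusted SE of the difference is the square root of that, times √(2/99). The share of variance removed is r² = slope² / [(1 − ρ) × 2.659 + ρ × 8.608], and the adjusted SE is the unadjusted SE times √(1 − r²).

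| ρ | Shift at 1 SE of baseline difference | Unadjusted SE | Shift / SE | Variance removed | Adjusted SE |
|---|---|---|---|---|---|
| 0.3 | 0.025 | 0.060 | 0.4 | 18% | 0.054 |
| 0.5 | 0.042 | 0.067 | 0.6 | 38% | 0.053 |
| 0.7 | 0.058 | 0.074 | 0.8 | 62% | 0.046 |

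If the correlation starts at 0.7 and decays by a factor of 0.9 or 0.8 per year, the slope is 1.77 or 1.52 and the variance removed is 51% or 41%, inside the same range.

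**Step 5: what this does to the test.** Given a baseline difference of k standard errors and no treatment effect, the unadjusted QALY statistic is normal with mean r × k and variance 1 − r². At k = 1.96 the two-sided false-positive rate is about 11%, 17% or 25% for ρ = 0.3, 0.5 and 0.7. At k = 0 it is about 3%, 1% or 0.1%. Averaged over k it is the nominal 5%.

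**The case against.** The strongest reply is that nothing invalid is planned. Allocation is randomised 1:1, so the unadjusted comparison is unbiased and its SE already covers chance differences at baseline. The article does not use the word unadjusted, it is a condensed account, and a fuller economic analysis plan may add the covariate. The outcome is secondary, and the other ratio does not use QALYs.

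Most of this stands, and it rules out several stronger readings that a reader might infer:

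- *That the comparison is biased, or that imbalance is to be expected.* The expected baseline difference is zero; only its spread is not. The harm is conditional on the difference that occurs, plus lost precision.
- *That a baseline difference carries over in full for 36 months because the curve starts there.* The carry-over is partial and runs through within-patient correlation (Steps 1 and 2).
- *That a non-parametric test cannot adjust.* The article names no particular test, and rank-based covariate adjustment exists. The fair statement is that none is named and that such tests, as usually applied, do not adjust.
- *That the sign of the ratio will turn on baseline luck.* The documents give no expected QALY gain to set against these shifts.
- *That the ratio is stated to be unadjusted.* The Economic evaluation section does not name the estimator. This is an inference from its use of the cost and effect results.

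The reply does not remove the point itself. The article settles how QALYs are compared, by a test chosen on normality, and reserves its only stratified analysis for the binary endpoints. A better estimator is available from data already collected.

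**Conclusion.** The point holds as an improvement in efficiency and robustness to a secondary economic outcome, not as an error that invalidates the analysis. The direction is sound whenever repeated EQ-5D scores correlate within patients. The size depends on the assumed SD, correlation and number evaluable, and the shift varies more than twofold across the range examined (0.025 to 0.058 QALY at one standard error of baseline difference). Nothing here touches the recurrence endpoint, the sample size or the cost per recurrence-free patient.

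**What to change.** Replace the sentence on comparing QALYs with an estimation rule. At 6 and 36 months, estimate the mean QALY difference by regression on arm and baseline EQ-5D index, optionally with the polyp size and location strata. Handle non-normality with bootstrap confidence intervals rather than by switching to a different test. State in the Economic evaluation section that the adjusted mean difference enters the cost-per-QALY ratio, and report the unadjusted difference as a sensitivity analysis. If an economic analysis plan already specifies this, align the published wording with it.

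The cost is about one sentence in each of the two sections, settled before the data are analysed. No extra data, visits or patients are needed.

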## Background

Resection of colorectal adenomas has shown to lower the mortality rate due to colorectal cancer with 60 % [1]. Especially large adenomas maintain a high risk of progression to invasive cancer, underlining the importance of adequate resection [2]. Endoscopic resection of large adenomas has been proven to be feasible and safe, with less morbidity, mortality and costs compared to surgical resection [3]. Endoscopic resection of non-pedunculated adenomas is most often performed using the ‘lift-and-cut’ endoscopic mucosal resection (EMR) technique [4]. However, in adenomas larger than 2 cm in size EMR can often only be performed in a piecemeal fashion (pEMR) due to the limited size of the snare, difficulty to position the endoscope, and often extension of the polyp over one or multiple folds [5, 6]. Although safe, piecemeal resection lowers the reliability of assessing the dysplasia free resection margins (R0 resection) at histology. This is also reflected by the relative high recurrence rate at follow-up colonoscopy after EMR ranging between 12-16 %, and even increasing up to 30 % in non-pedunculated polyps exceeding 40 mm in size [7, 8].

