## Methods

This randomized clinical trial will randomize between ESD and EMR in patients with large distal non-pedunculated colorectal adenomas. Seventeen Dutch hospitals will participate, including three academic and fourteen non-academic hospitals. The flowchart of the design of the MATILDA-trial is displayed in Fig. 1.

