### Recruitment and randomization

Initial recruitment of patients will be performed by the local coordinating investigator of the participating center. When a polyp is found at index colonoscopy that fulfills the inclusion criteria, exclusion criteria will be checked. In presence of exclusion criteria, this will be registered in the screening log. In absence of exclusion criteria, the local coordinating investigator will provide oral and written information on the study to the patient. Patients will have as much time as they like to think about participation and will have the chance to ask any questions on the study. Thereafter the informed consent form is signed. In case of non-participation, this will be recorded in the screening log (see Fig. 1). Independent computer-based randomization will be performed (Castor Electronic Data Capture (EDC), CIWIT b.v.) in a 1:1 ratio. Randomization will be stratified by the size of the polyp (20-30 mm, 31-40 mm, >40 mm), localization (rectum, sigmoid, descending colon) and center using block sizes of five per block. Due to the nature of the treatment, neither patients nor endoscopists participating in this study will be blinded.

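### The cost and QALY comparisons name none of the randomisation factors, so the cost difference feeding the ICER may be somewhat less precise than it could be (minor, optional)

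*Protocol article*

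**What the plan says.** Under Recruitment and randomization, the protocol article states: "Randomization will be stratified by the size of the polyp (20-30 mm, 31-40 mm, >40 mm), localization (rectum, sigmoid, descending colon) and center". The Methods opening adds that "Seventeen Dutch hospitals will participate".

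The Data analysis section treats the outcomes in two ways:

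- Recurrence, R0 resection, surgical referral and complications "will be compared using a stratified analysis with a test for binary outcomes". The factors are not named; that they are the randomisation factors is an inference, though a natural one.
- Costs at 6 and 36 months: "Costs estimates will be compared between both arms using a non-parametric test". QALYs get a non-parametric test if they are not normally distributed. Neither sentence mentions a stratum or covariate.

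The Economic evaluation section then combines cost and effect differences into ICERs at both horizons and mentions no adjustment.

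On the link between size and outcome, the Background gives recurrence after EMR as 12-16% overall, "even increasing up to 30 % in non-pedunculated polyps exceeding 40 mm in size". The Follow-up colonoscopies section makes recurrence the trigger for further colonoscopies, repeat resections and possible surgical referral. The Secondary outcomes section counts resources used for recurrence and surgical referral as cost data.

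**The concern.** Cost-effectiveness is half of the stated aim, and the mean cost difference is the numerator of every ICER. Polyp size is a randomisation factor that, on the article's own figures, affects recurrence after EMR and hence follow-up cost. The article carries stratification into the analysis of the binary outcomes but states a different method, without strata, for costs and QALYs.

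Two things are at stake, both about precision:

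1. **Interval width.** To the extent that stratified allocation balances a factor that predicts cost, an unadjusted standard error still contains variation that the design has removed. The interval is then too wide and the test conservative.
2. **Noise in the estimate.** To the extent that allocation does not balance that factor, the remaining chance imbalance passes into the cost difference.

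These two effects share the same variation between them, so they cannot both apply in full.

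**Working it through.** **The plan's own figure.** The sample size assumes that "the recurrence rate is 2 % in the ESD group and 12 % in the EMR group", and "With a power of 80 % and a two-sided α of 0.05, the total number of patients needed is 198". With unpooled variance, (1.960 + 0.842)² x (0.12 x 0.88 + 0.02 x 0.98) / 0.10² = 98.27, so 99 per arm and 198 in total, as stated. Then 198 x 1.07 = 211.9, which gives the 212 stated. This point changes none of these figures. The article gives no precision target or variance for cost.

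**Standard error if the strata predict cost.** Let R² be the share of within-arm cost variance explained by the adjustment factors. R² is assumed throughout.

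- Ratio of adjusted to unadjusted standard error = √(1 − R²).
- Equivalent sample size = 198 / (1 − R²).
- Power, if the unadjusted comparison had 80% (also assumed; the trial is not powered on cost) = Φ((1.960 + 0.842)/√(1 − R²) − 1.960).

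| R² (assumed) | SE ratio | Reduction in SE | Equivalent N | Power |
|---|---|---|---|---|
| 0.02 | 0.990 | 1% | 202 | 80.8% |
| 0.05 | 0.975 | 2.5% | 208 | 82.0% |
| 0.10 | 0.949 | 5% | 220 | 84.0% |
| 0.20 | 0.894 | 11% | 248 | 87.9% |

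**What the documented link alone might support.** Assume 25% of polyps exceed 40 mm (not in the article).

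- EMR recurrence 12% overall and 30% above 40 mm: the rest recur at (0.12 − 0.25 x 0.30)/0.75 = 6%, a gap of 24 points. With overall recurrence at 16%, the rest recur at 11.3%, a gap of 18.7 points.
- ESD recurrence 2%, either unrelated to size (gap 0) or with the same relative gradient as EMR (gap 4 points when EMR is 12%).
- For a common size effect, the explained share = 0.25 x 0.75 x (mean gap)² / (mean within-arm variance).
- Low end: 0.1875 x 0.0933² / [(0.1344 + 0.0196)/2] = 0.00163/0.077 = 2%.
- High end: 0.1875 x 0.14² / [(0.1056 + 0.0196)/2] = 0.00368/0.0626 = 6%.

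So size explains about 2-6% of the variance in recurrence itself. If cost followed recurrence alone, the gain would be about 1-2 points of power.

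**Does the allocation already balance size?** The strata number 3 x 3 x 17 = 153 for 212 patients, about 1.4 per cell, so most blocks of five stay incomplete. A simulation of this scheme used assumed inputs: 25% of polyps above 40 mm, uneven centers, and each block split 3:2 or 2:3. The between-arm difference in the share above 40 mm had an SD of 4.5-4.9 percentage points. Stratifying by size alone gave 2.7, and simple randomisation gives √(0.25 x 0.75 x 2/106) = 5.9. Balance on size is therefore partial.

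With assumed log-normal costs under the same scheme, adjusting for size and localization lowered the true SD of the cost difference from 206 to 203 at R² about 0.07, and from 258 to 243 at about 0.19. The reported standard errors fell by 2% and 8%. With no link between size and cost, the penalty was under 1%.

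**Price of the extra terms.** With p covariates, the SE ratio is about √[(1 − R²)(N − 3)/(N − p − 3)]. With N = 198:

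- Size and localization only (p = 4): break-even is at R² about 0.02 (√(0.98 x 195/191) = 1.000).
- Adding 16 fixed center terms (p = 20): break-even is at R² about 0.10 (√(0.90 x 195/175) = 1.001).

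**The case against.** The strongest reply is that the point rests on silence. The article does not say unstratified, a stratified rank test is also non-parametric, and covariates for economic outcomes are often left to a fuller document. This carries weight and limits the severity. It does not remove the point, because the same section raises stratification, attaches it to four named binary outcomes, and then states a separate method for costs.

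The second reply is that the gain may be negligible. That stands: no cost variance or R² is given, and the documented size-recurrence link alone suggests a gain at the low end. A rank test also yields no mean cost difference, so the precision argument concerns the difference used in the ICER rather than the quoted test.

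A reader might also infer stronger points that the article does not support:

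- **That larger polyps cost more because they take longer to resect.** This is plausible, but the Background relates procedure time to technique only.
- **That adjusting for recruiting center removes hospital cost differences.** Under Study setting, patients allocated to ESD in a center without an experienced endoscopist are referred elsewhere, so the recruiting center is not always the treating hospital.
- **That large chance imbalances in polyp size are common.** Calculating as if randomisation were simple overstates them, and chance imbalance is ordinary sampling error, not bias.
- **That QALYs would gain similarly.** No stratum is linked to QALYs in the article. They are included for consistency within the ICER.

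**Conclusion.** The point holds as a minor, optional efficiency improvement on secondary outcomes. The stated cost and QALY comparisons name no randomisation factor, although size is tied to recurrence after EMR and so to follow-up cost. If the strata predict cost, the unadjusted cost difference has an interval that is too wide and, because balance on size is only partial, a slightly noisier estimate. For an assumed R² of 0.02 to 0.20 the standard error would fall by about 1% to 11%; with no link to cost there is no gain.

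It would be wrong to conclude that the planned comparison is biased or invalid: an unadjusted randomised comparison is valid and at worst conservative. The primary endpoint, its analysis and the sample size are not affected.

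**What to change.** In the Data analysis section, state that the 6- and 36-month mean cost differences and mean QALY differences will be estimated by regression on arm, polyp-size category and localization. Include center as a random effect rather than 16 fixed terms, and use bootstrap confidence intervals. In the Economic evaluation section, state that these adjusted differences enter the ICERs, with the unadjusted comparison kept as a sensitivity analysis.

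The cost is a change of wording and a few extra model parameters. All three factors are known at randomisation, so no new data are needed.

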For this reason endoscopic submucosal dissection (ESD) was developed in Japan, a technique that enables to achieve en-bloc resection even in large polyps [9]. Several retrospective observational studies compared EMR and ESD. A recent meta-analysis pooled the results yielding a total of 2299 lesions [10]. Although studies were biased by baseline differences with special regard to tumor location and polyp size due to lack of a randomized design, results are promising. Rates of en bloc resection and radical resection were much higher, and the rate of recurrence was much lower in the ESD-group (91.7, 80.3 and 0.9 % respectively) than in the EMR-group (46.7, 42.3 and 12.2 % respectively). This benefit comes at the expense of an about three-fold longer procedure time and more complications (perforation rate 5.7 % versus 1.4 %). However, this safety profile may be favorable in the distal colon, given the lower risk for complications as compared to proximally located polyps [11]. We hypothesize that the prolonged procedure time will initially result in higher healthcare costs, but that this time-investment will earn itself back on the long-term due a higher number of R0-resections and lower recurrence rates with less need for repeated procedures. If indeed ESD proves to be (cost-)effective on the long-term, burden of extra colonoscopies and repeated procedures can be prevented for patients in the future. It is important to address this gap in the current knowledge, especially now that screening programs have been widely introduced and the detection of large adenomas will further increase.

Therefore, the aim of this randomized clinical trial is to evaluate the effectiveness and cost-effectiveness of ESD against EMR on both short (i.e. 6 months) and long-term (i.e. 36 months) for large (>20 mm) distal non-pedunculated adenomas.

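### The non-parametric cost test, read in the ordinary way as a rank test, does not test the mean cost difference that the ICERs use, and the two can disagree, mainly at 36 months

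*Protocol article*

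**What the plan says.** All references are to the protocol article.

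- **Cost test (Data analysis).** "Costs estimates will be compared between both arms using a non-parametric test". No normality condition is attached. Costs "will be compared for the 6-month follow-up (i.e. short-term) and the 36-month follow-up (i.e. long-term), respectively", and the section closes by saying that a p-"value of < 0.05 will be considered significant".
- **QALY test (same section).** "QALY estimates will be compared between both arms using non-parametric test when not normally distributed". Here the non-parametric test is a conditional fallback.
- **Summaries (same section).** "not-normally distributed variables will be expressed as median (interquartile range").
- **Economic evaluation.** Results are "expressed as incremental cost-effectiveness ratios (ICER) showing additional costs per recurrence free patient", and also as incremental cost per incremental QALY. Sensitivity and scenario analyses are announced. No resampling method and no interval for the mean cost difference is named.
- **Background.** ESD is expected to cost more at first because the procedure takes about three times as long, but "this time-investment will earn itself back on the long-term" through more R0 resections and fewer repeat procedures.

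**The concern.** The numerator of an ICER is a difference in arithmetic mean cost. A rank test asks whether a patient in one arm tends to cost more than a patient in the other; how expensive the dearest patients are hardly matters to it. The two questions part company when one arm costs moderately more in nearly everyone and the other has a small, expensive tail. That is the pattern the Background predicts: a higher index cost for most ESD patients, and repeat treatment in a minority of EMR patients.

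A rank test would then mostly register the index cost and give little weight to the later savings. A report could state that ESD is significantly more costly next to an ICER whose numerator is zero or negative. Cost-effectiveness is a stated aim of the trial, so readers and payers would have to choose between two conflicting statements about cost.

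**Working it through.** **The plan's own figure.** The article gives no figure for costs. Its sample size supplies the number per arm and does reproduce: n = (1.96 + 0.8416)² × (0.12 × 0.88 + 0.02 × 0.98) / 0.10² = 98.3, so 99 per arm and 198 in total; 198 × 1.07 ≈ 212.

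**Inputs from the article.** 99 evaluable patients per arm; recurrence 12% (EMR) and 2% (ESD); two-sided 0.05.

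**Assumed inputs.** Mean EMR index cost EUR 2000; mean ESD index cost EUR 2000 plus a gap; lognormal index costs with coefficient of variation (CV) 0.3 or 0.5; a fixed extra cost per recurrence (the tail).

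**Condition for equal true means.** gap = tail × (0.12 − 0.02) = 0.10 × tail.

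**Equal true means, 4000 simulated trials per scenario.** The nominal rate for falsely calling ESD dearer is 2.5%.

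| Cost per recurrence | Index gap | Mann-Whitney calls ESD dearer, CV 0.3 | Same, CV 0.5 | Welch rejects, either direction |
|---|---|---|---|---|
| 2000 (1 × EMR index) | 200 | 11% | 4% | 5% |
| 4000 (2 ×) | 400 | 66% | 19% | 5% |
| 8000 (4 ×) | 800 | 99.9% | 81% | 5 to 6% |

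Other runs of the same model agree to within simulation error: about 5 to 13% in the first row, 68% in the second at CV 0.3, and 99.9% and 82% in the third.

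**ESD truly cheaper.** With a gap of 800 and a tail of 12000 (six times the EMR index cost), the true difference is 800 − 0.10 × 12000 = −400. At CV 0.3 Mann-Whitney calls ESD dearer in 99.9% of trials. In 82% of trials it does so although ESD's observed mean cost is equal or lower in that same trial.

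**A benign case.** With a gap of 800 and a tail of 2000, ESD is truly dearer by 800 − 0.10 × 2000 = 600. At CV 0.3 Mann-Whitney rejects in about 100% and Welch in 99.7%, so the tests agree.

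**A second set of assumptions.** Eighteen equal-mean scenarios were run with 1000 trials each: EMR base cost 1000 units; recurrence costing 1500 or 3000; no surgery, or surgery at 10000 (5% vs 2%) or 15000 (8% vs 2%); CV 0.2, 0.4 or 0.6. Mann-Whitney called ESD dearer in 9.3% to 100% of trials, and in at least 70% in 15 of the 18. The three milder results (9.3%, 16.6%, 35.8%) all had no surgery and CV 0.4 or 0.6. Welch called ESD dearer in 3.1% to 6.2%.

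**The case against.** Four points on the other side carry weight.

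1. **The article never says rank.** A permutation or bootstrap test of mean costs is also non-parametric and would escape the criticism. The article condenses a fuller protocol and perhaps a SAP, either of which may name the test. A reader might infer that a Mann-Whitney test is prescribed; the text does not establish that. The rank reading is still the ordinary one: the same section summarises skewed variables by medians, uses the term as the fallback for non-normal QALYs, and names no resampling of means. If means were intended, the wording needs to say so.
2. **The size rests on chosen costs.** In the severe scenarios a recurrence costs four to six EMR procedures. The Follow-up colonoscopies section does not obviously support such an average: every patient has the 6-month colonoscopy anyway, residual disease is resected there, and surgical referral comes only after up to three endoscopic attempts. The main model also gives ESD no complication tail, although the Background cites perforation in 5.7% versus 1.4%. This stands, and is why the mild cases are shown with the severe ones.
3. **The reach is limited.** No section ties the cost-effectiveness conclusion to the cost p-value. A reader might infer that the ICERs or the main trial result would be wrong; the ICER point estimates, the primary endpoint and the sample size are all untouched.
4. **The horizons differ.** At 6 months the trial itself expects ESD to cost more and later repeat treatment has not accrued, so ranks and means should mostly agree in direction. The issue is essentially one for 36 months.

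**Conclusion.** The point holds in a limited form. Read in the ordinary way, the planned cost test addresses a different quantity from the ICER numerator, and the trial's own hypothesis describes the setting in which the two can disagree. The disagreement is slight if a recurrence costs about one EMR procedure (about 5 to 13% of trials wrongly calling ESD dearer). At two to four times that cost it is about 67% to over 99% with CV 0.3, and 19% to about 82% with CV 0.5. A test of means stays near 5% throughout. These figures depend on assumed unit costs and on the equal-means condition.

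Two stronger readings are not supported. One is that the plan will nearly always call ESD falsely dearer: that needs an expensive tail that happens to offset the index gap. The other is that QALYs are to be rank-tested outright: the text makes that test conditional on non-normality, so the same issue arises for QALYs only if that condition is met.

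**What to change.** In the Data analysis section, replace the cost test, and the conditional QALY fallback, with the difference in arithmetic means between arms and a bootstrap 95% confidence interval, at 6 and at 36 months. Resample cost-effect pairs jointly within arm, so that the same run gives the uncertainty of both ICERs. Prefer a bias-corrected interval and check its coverage: in one heavily skewed equal-means scenario a plain percentile bootstrap rejected in 8.8% of trials. Medians and rank tests may stay as descriptive results. If a resampling test of means was already intended, one clarifying phrase is enough.

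The cost is a change of wording, a little programming and a wider interval for costs. No new data or patients are needed. The change should be made before costs are analysed by arm.
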